#### 10. Interview is upsetting/distressing for the participant.

Pre-mitigation risk:

Severity: 3. Likelihood: 1. Risk: 3 (Low).

Mitigation: Distress protocol (Draucker, Martsof and Poole, 2009) will be followed should any distressing issues arise during the interview process.

Post-mitigation risk:

Severity: 2. Likelihood: 1. Risk: 2 (Low).

Service user group feedback suggested that the study processes were acceptable and did not pose an unacceptable risk and burden.

## RISKS TO RESEARCHER

1. Working in the diabetes department in-hospital will carry the risk of increased exposure to COVID-19.

Pre-mitigation risk:

Severity: 2. Likelihood: 2. Risk: 4 (Medium).

Mitigation:

The researcher already works in hospital – no increased risk from baseline. The researcher is trained and fully up-to-date with the use of PPE and the latest PHE guidance on social distancing and hand-washing. The researcher has been risk-scored for COVID-19 by STHK and has been deemed low risk, taking into account age, gender, ethnicity, shielding status, childcare arrangements, underlying health conditions and work environment.

Post-mitigation risk:

Severity: 1. Likelihood: 1. Risk: 1 (Low).

## OTHER RISKS.

1. Identification and screening of participants (use of patient-identifiable data).

The national data-opt out service enables the public to opt-out of their confidential information being used for the purposes beyond their individual care and treatment. The public can change their national data opt-out choice at any time. National data opt-outs apply to a disclosure of confidential information when a researcher confirms they have approval from the Confidentiality Advisory Group (CAG) for use of patient-identifiable information, unless, as is the case with this project, the researcher is already an existing member of the study population's existing clinical care team.

All NHS trusts are compliant with the national data-opt out policy as of 31/3/2020.

Ethical approval by Edge Hill University Health Research Ethics Committee, and the Health Research Authority is required prior to research commencement. Use of contact details of patients who have been referred to the Department of Diabetes and Endocrinology at St Helens and Knowsley Teaching Hospitals NHS Trust (for the purposes of contacting a patient to consent) is allowed as the researcher is a member of the existing clinical care team.

Service user group feedback has been sought on the use of patient-identifiable information for the purposes of contacting potential research participants. General feedback from the group, including people with diabetes, was that contacting patients for the purpose of research recruitment (as a member of the patient's existing clinical care team) is justifiable as the knowledge gained from the research is hoped to improve patient care.

## 2. Consent.

Good clinical practice (GCP) guidelines will be followed throughout the study. The researcher has received online training and certification from the National Institute of Health Research (NIHR) on GCP.

The researcher works as a healthcare professional within St Helens and Knowsley Teaching Hospitals NHS Trust (research sponsor). The researcher will maintain clinical knowledge by undertaking routine clinical work in diabetes, endocrinology and general internal medicine. The researcher will maintain full registration with the General Medical Council with a licence to practice. The research will maintain medical indemnity with the Medical Defence Union.

## **8.2 Research Ethics Committee (REC) and other Regulatory review & reports**

Before the start of the study, a favourable opinion will be sought from Edge Hill University REC and the Health Research Authority (HRA).

### **8.2.1 Regulatory Review & Compliance**

Before any site can enrol patients into the study, the Chief Investigator/Principal Investigator or designee will ensure that appropriate approvals from participating organisations are in place. For any amendment to the study, the Chief Investigator or designee, in agreement with the sponsor (STHK) will submit information to the appropriate body in order for them to issue approval for the amendment. The Chief Investigator or designee will work with STHK Trust R&D so they can put the necessary arrangements in place to implement the amendment to confirm their support for the study as amended.

### **8.2.2 Amendments**

If a substantial amendment to the protocol or associated study documents is required, the sponsor must submit a valid notice of amendment to the REC for consideration. The REC will provide a response regarding the amendment within 35 days of receipt of the notice.

If applicable, other specialist review bodies (e.g. Edge Hill University Health Research Ethics Committee) need to be notified about substantial amendments in case the amendment affects their opinion of the study.

The requirement for amendments will be decided by the researcher and the researcher's supervisory team. If amendments to the protocol or associated study documents is required, changes to the documents will be made by the research student with advice from the supervisory team. Changes will be communicated to the sponsor (STHK). It is the sponsor's responsibility to decide whether an amendment is substantial or non-substantial for the purposes of submission to the REC.

Amendment history will be tracked. Study documents will be held in a hierarchical file system. Documents will be named in the following fashion:

'study title' - 'document name' - 'document version number (1.0.0)' - 'document creation/update date (YYYY-MM-DD)'.extension

Document version and date will be displayed in the file name and on each page of the document. Ratified master copies of the documents will be held as read-only copies on a cloud-shared NHS computer drive. Document version numbers are displayed as 'Major.Minor.Revision'. The first version of a document would be '1.0.0' with revisions displayed as '1.0.1', minor adaptations as '1.1.0' and major changes as '2.0.0'. Once updated documents have been ratified, old copies of the documents will be archived and the new copies will replace them in the master file. Document revisions will be recorded in a separate document.

### 8.3 Peer review

Internal and external independent, proportionate (to the size and complexity of the study) and expert (reviewers should have knowledge of the relevant discipline and/or expertise to assess the methodological aspects of the study) peer review will take place and be submitted to the sponsor. The internal and external peer review documents are included in [Section 11.1](#) 'Appendix 1 – Required Documentation'. The internal peer reviewer (Consultant Physician/Diabetologist) approved the study protocol. The external peer reviewer (Professor of Medicine and Honorary Consultant Diabetologist) had a few minor comments and one major comment. These are summarised below, with accompanying amendments.

1. Clarify recruitment population and stratification (minor).  
⇒ [Section 7.1.1](#) 'Inclusion Criteria' updated.
2. Provide a stronger rationale for setting higher explicit HbA1c targets (major).  
⇒ [Section 2](#) 'Rationale' and [section 5.1](#) 'Study A - Study Design' updated.
3. Amend the HbA1c study leaflet infographic to include levels of HbA1c considered adequate by guidelines and non-diabetic HbA1c levels (minor).  
⇒ [Section 11.1](#) 'Appendix 1 – Required Documentation' HbA1c Leaflet amended.
4. Consider including healthcare professionals from outside STHK in interviews (minor).  
⇒ Following discussion with the supervisory team, it was felt that we could potentially include healthcare professionals if the study fails to recruit suitable numbers locally.

University research approval processes (research project registration) suggested the inclusion of additional qualitative aspects of the study in the event that poor recruitment is seen in the quantitative aspects of the project (Study A). Study D was added to the protocol to address these concerns.

### 8.4 Patient & Public Involvement

Service user (SU) group feedback has been sought on the research proposal and the patient-facing study documents (participant information sheets, consent forms, leaflets, invitation letters). The service user group consists of a range of people from the general public, people with diabetes and expert patients. Feedback was received via email and video call. Documents have been updated with respect to the received comments:

- Comments suggested to clarify in the participant information sheet that taking part in research will not affect patient care. It is now explicit in the patient information sheets that involvement in the research does not affect their clinical care.

- One member on the SU group mentioned that the section on consent in the participant information sheets should be expanded upon to make it clear that individual consent is required and can be withdrawn at any time.
- Comments suggested evaluation of barriers to participation in those declining entry into the main study. 'Study D' has been added to the protocol to address this point.

Service user group feedback was sought on the acceptability of using patient identifiable data in the study without prior consent (namely for the purpose of contacting individuals to invite them to take part in the research). Feedback suggested that the use of patient-identifiable data for this purpose was reasonable.

Specific comments:

- "would be happy to be contacted" (person with diabetes)
- "seems reasonable"
- "the invitation letter could improve recruitment if it comes from the consultant"
- "I wouldn't mind being contacted out of the blue for this project"
- "As long as it's highlighted that it is optional and not affecting healthcare"
- "it's important that you regularly update your participants as to the research progress and results"
- "it would be interesting if you followed-up non-responders to see why they didn't want to take part"

The SU group also suggested that it is important to regularly update people involved in the research. Following completion of the research, dissemination of the results to involved participants and the local diabetes service user group is planned.

## **8.5 Protocol compliance**

Publication of the protocol is planned to ensure greater transparency of the research process and also informs the research community about what research activity is currently being carried out in different fields, preventing unnecessary duplication of work and encouraging collaboration between research groups. Accidental protocol deviations can happen at any time. These will be adequately documented on the relevant forms and reported to the Chief Investigator and Sponsor immediately.

## **8.6 Data protection and patient confidentiality**

All data obtained will be anonymised for person- and place-identifiable information during transcription/database input by removal of direct identifiers. The secure holding of all data during the study period will be on password-protected NHS computers with NHS-level data encryption. Transfer of study data between computing devices will be either with an NHS-encrypted USB drive or a secure N3 (NHS network encrypted) email. Non-electronic data (e.g. consent forms, completed questionnaire) will be held in a secure file in a separate locked research office on NHS sites when not in use. Audio-

recording data (.mp3/.wav) will be stored securely on a password-protected recorder device in a separate locked research office on NHS sites when not in use. Audio recordings will be held separately to signed consent form documents. All paper documentation will be held in a separate, locked file in a locked research office. Any detailed, identifiable free-text responses from surveys or semi-structured interviews will have their meaning generalised during transcription to prevent disclosure. Direct identifiers in all data obtained will be replaced with a code. Identifier code data will be located in a password-protected Microsoft Excel document on NHS-encrypted computers. Patient identifiers will be held in a separate, password-protected database and linked through a unique study code. Separation of patient identifiers from other data will be at the point of entry into the database.

University and Health Research Authority ethical approval will be obtained prior to recruitment/commencement of data collection.

### **8.7 Indemnity**

Sponsor indemnity: STHK NHS R&D indemnity.

Investigator indemnity: the researcher and chief investigator are individually indemnified personal medical indemnity.

### **8.8 Access to the final study dataset**

The final dataset will be accessed by the research team. All anonymised data collected could be of potential value for future research. As such, the collected, anonymised computer data will be submitted to the Edge Hill University research data repository for use upon completion and publication of the research. Participants will be consented for this.

Physical copies of data will be kept for the duration specified by St Helens and Knowsley Teaching Hospitals NHS Trust (STHK) Research Guidelines, at which point further retention of the data can be reviewed. Consent forms will be kept for as long as the research data are retained in the data repository. Following the completion of the research, they will be digitised and stored securely (encrypted) with the university. At this point, original physical copies will be destroyed securely (<https://www.ukdataservice.ac.uk/manage-data/legal-ethical/consent-data-sharing/consent-forms>).

### **8.9 Progression criteria (go/no-go)**

A green (proceed: there are no concerning issues that threaten the success of a future trial), amber (amend: where there are remediable issues, thereafter proceeding with caution), red (stop: there are intractable issues which cannot be remedied) system will be used to determine progression to a main trial.

Criteria informing the green/amber/red system will use:

a. Screening.

⇒ Ensuring a sufficient pool of patients to screen will be key in achieving the required sample.

In STHK, six face-to-face diabetes clinics run per week with eight patients per clinic. Usually, at most, there are three 'Did Not Attends' (DNAs) or cancellations, leaving a usual minimum of five patients per clinic. This leaves 130 patients/month to screen.

b. Eligibility.

⇒ Determination of the expected eligibility rate of patients will allow for an estimation of the likelihood that investigators will have enough participants to recruit.

For study A, it is estimated that 25% of screened patients will be eligible to participate in the study (cf. other diabetes trials) (Steiner et al., 2015, Neal et al., 2017, Wiviott et al., 2019). This means an estimated 32 patients/month will be eligible to study entry.

c. Recruitment.

⇒ Recruitment is the most commonly used criterion in establishing whether a feasibility study or pilot study should progress to a main trial. Suggested methods of determining adequate recruitment are to compare expected versus actual recruitment per centre per month.

For this study, the recruitment period is planned to take place over a 4-month period. Fifty participants are required for the quantitative aspects of study A according to the protocol. Therefore a recruitment rate of 13 participants/month over four months will result in achieving the desired sample.

It is estimated that 70% of eligible patients will agree to study enrolment (cf. other diabetes trials) (DAFNE Study Group, 2002, Davies et al., 2008). This means 22 patients/month of the 32 eligible patients are predicted to enrol.

d. Protocol non-adherence.

⇒ More commonly used in the clinical trials of investigational medicinal products (CTIMPs), the focus of evaluation of protocol non-adherence is on adherence to the trial intervention. Types of non-adherence are 'cross-over' or 'off-protocol intervention'. Cross-over is where a participant does not receive their allocated intervention, instead receiving an alternate intervention. This will reduce the power of the study. Off-protocol intervention is where another intervention which is not included in the protocol is used. Non-adherence may arise due to side effects of the intervention or problems with the acceptability of the intervention.

In this study, cross-over and off-protocol intervention episodes will be monitored and recorded.

e. Outcome data.

⇒ Monitoring the quality and completeness of short-term outcome data provides valuable insight into issues which can be addressed for the main trial. Missing or incomplete data will impact upon the required sample size. Loss of data in this way can be due to attrition, acceptability of the outcome assessment protocol or the outcome measurement tools themselves. Generally, loss to follow-up should be < 20% to reduce threats to trial validity (Dettori, 2011). Greater than 60% of participants would need to provide response data to enable a trial to be powered to show an effect and reduce response bias (Fincham, 2008).

Considering these criteria, reasonable progression criteria ('green') for study A are:

- Identification of at least 19 eligible patients/month through screening.
- Recruitment of at least 13 patients/month.
- Monitoring of cross-over and off-protocol intervention episodes for significant protocol deviation.
- Retention of ≥ 80% at follow-up.
- Response rate of ≥ 60% for PROMs.

Failure to meet these criteria result in an amber situation. Identifiable remediable adjustments to allow trial progression will be identified. Failure to meet the progression criteria without the identification of remediable changes may result in a red situation where the trial will be prevented from progressing.

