## **7.2 Sampling**

### **7.2.1 Size of sample**

Study A: Influential papers (Julious, 2005, Sim and Lewis, 2012) on the sample size requirements for feasibility studies have suggested between 24 and 50 participants are required to estimate the standard deviation of an outcome measure (often needed in the calculation of sample sizes in larger studies).

Given an estimated study participation rate of 70% of those eligible, based on participation rates of eligible patients in the DAFNE (DAFNE Study Group, 2002) and DESMOND (Davies et al., 2008) trials, 72 eligible patients will be selected for entry into the study in order to enrol 50 participants ( $70\% \times 72 \approx 50$ ).

Depending on eligibility and recruitment rates, the sample size may have to be adapted.

Study B: A stratified (by type 1 and type 2 diabetes), purposive estimated sample of 15 participants will be required. Sample adequacy will be determined using the concept of information power, described by

Malterud et al. (2016). Estimates of sample size required in similar studies suggest a requirement of 10 – 15 participants. Adjustments to sample size may be required during the study, depending on the information power of the sample.

Study C: A convenience sample of 15 participants will be recruited. Determination of sample adequacy as per study B. Adjustments to sample size may be required during the study, depending on the information power of the sample.

Study D: A stratified (by type 1 and type 2 diabetes), purposive estimated sample of 15 participants will be required. Sample adequacy will be determined as per study B. Estimates of sample size required in similar studies (Taylor et al., 2007, Harrop et al., 2016, Hughes-Morley et al., 2016) suggest a requirement of 10 – 39 participants. Adjustments to sample size may be required during the study, depending on the information power of the sample.

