### **7.2.2 Sampling technique**

Study A: Patients due to attend new patient diabetes clinic at St Helens Hospital Diabetes centre will be screened for entry into study A. Patients meeting eligibility criteria will be invited to enter the study by postal letter with an included participant information sheet (see appendix 1). Invites will be followed up with telephone calls. Patients who express interest in taking part in the study will be approached for recruitment into the study on attendance to their diabetes clinic appointment. Sampling will continue until the required number is achieved.

Study B: fifteen participants who took part in study A will be recruited in a stratified (for type 1 and type 2 diabetes), purposive manner.

Study C: a convenience sample of 15 healthcare professionals directly involved in secondary care diabetes services (including consultant, specialist nurse, nurse consultant, dietician, specialist registrar and specialty doctor grades) will be selected for interview.

Study D: fifteen patients who were eligible for and declined participation in study A will be recruited in a stratified (for type 1 and type 2 diabetes), purposive manner.

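### The green recruitment line of 13/month is 50/4 = 12.5 rounded up, so enrolling the required 50 in the planned 4 months literally scores amber

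*Protocol*

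**What the plan says.** Protocol section 8.9, part c, sets out the recruitment need. It states that "Fifty participants are required for the quantitative aspects of study A according to the protocol" and that "the recruitment period is planned to take place over a 4-month period". From these it concludes: "Therefore a recruitment rate of 13 participants/month over four months will result in achieving the desired sample".

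The list of green criteria at the end of section 8.9 then uses the same figure as a threshold, "Recruitment of at least 13 patients/month", beside an eligibility threshold, "Identification of at least 19 eligible patients/month through screening". The scoring rule follows: "Failure to meet these criteria result in an amber situation".

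On when enrolment ends, section 7.2.2 says for Study A: "Sampling will continue until the required number is achieved". Section 7.2.1 adds that the sample size may have to be adapted, but gives no rule for doing so. The protocol does not say whether the monthly rate is an average or a minimum for each month, what period it is taken over, or whether a fractional rate is rounded before scoring.

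**The concern.** Rounding 12.5 up to 13 is harmless when the figure is a planning rate, because recruiting at 13 per month does deliver 50 within 4 months. It is not harmless once the figure becomes a pass line. The sample is meant to stop at 50 and the timetable is 4 months, so the study as planned runs at 12.5 per month, which is below its own green line.

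Feasibility is the primary question of Study A, and section 8.9 itself calls recruitment the criterion most often used to decide on progression. A go/no-go rule should not mark down a study that delivers exactly what the protocol asked for. With the averaging period also left open, the same set of enrolments could be scored green or amber, depending on a choice made after the data are in.

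**Working it through.** **Inputs.** Required sample 50, recruitment period 4 months, green line 13 per month, 70% of eligible patients enrolling, forecast of 32 eligible and 22 enrolled per month (all section 8.9); sampling continues until the required number is reached (section 7.2.2).

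**1. Reproduce the plan's figures.**
- 50 / 4 = 12.5, rounded up to 13 per month. This matches.
- 13 / 0.70 = 18.57, rounded up to 19 eligible per month. This matches.
- 0.70 × 32 = 22.4, stated as 22 per month. This matches.

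So there is no arithmetic slip in the derivation. The issue is how the rounded result is used.

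**2. Score the plan against its own line.** 50 enrolled in exactly 4 months gives 50 / 4 = 12.5, and 12.5 < 13, hence amber.

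**3. What green requires under each averaging period.**
- Averaged to the 50th enrolment: 50 / 13 = 3.846 months. With 30.44 days per month this is 117 days, against 4 × 30.44 = 122 days, so about 5 days early.
- Averaged over a fixed 4 months: 13 × 4 = 52, two above the required sample.
- At least 13 in each of four months: again at least 4 × 13 = 52, so no split of 50 satisfies it.

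**4. Size of the effect, averaging to the 50th enrolment.** Assume, as the protocol does not, that enrolments follow a Poisson process with a constant true rate. The time to the 50th enrolment is then gamma-distributed with shape 50 and that rate.

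| True rate per month | P(50 by 3.846 months), the green line as written | P(50 by 4 months), the stated aim |
|---|---|---|
| 12.5 | 0.410 | 0.519 |
| 15 | 0.861 | 0.916 |
| 22 | > 0.999 | > 0.999 |

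The loss is about 11 percentage points at the planned rate, about 5 to 6 points at 15 per month, and nothing of note at the forecast rate. At 22 per month the sample fills in 50 / 22 = 2.27 months.

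**5. Knock-on to eligibility.** Starting from the unrounded rate, 12.5 / 0.70 = 17.86, rounded up to 18 per month rather than 19.

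**The case against.** The strongest reply is that patients come in whole numbers, that rounding a target rate up is ordinary and slightly conservative, and that the sentence in part c is true as written, since 13 × 4 = 52 covers 50. That stands for the planning sentence. It does not rescue the threshold, because nothing says that an observed 12.5 is rounded before it is scored.

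A second reply is that the cap of 50 is soft, since the sample size may be adapted and no maximum is stated. Enrolling two more would meet even the fixed 4-month reading. That is so, but a pass line should not depend on exceeding the sample the protocol says it requires.

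A third is that the averaging period is a detail for an analysis plan that is not shown here. That is fair for the averaging period. The figure of 13, however, is fixed in the protocol, and 50 in exactly 4 months misses it on either average.

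Two stronger readings are tempting but not supported:

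- A reader might infer that green cannot be reached at any recruitment speed. This holds only if the total is always divided by 4 months, or if 13 is demanded in every one of four months even after enrolment has closed. The protocol states neither. Averaged over the time recruitment is actually open, the forecast 22 per month is green.
- A reader might also set the 19 per month against section 7.2.1, where "72 eligible patients will be selected for entry into the study in order to enrol 50 participants", divide 72 by 4 to get 18, and conclude that a second green criterion can also give a wrong verdict. Section 7.2.1 attaches no time period to the 72, and nothing caps the number of eligible patients identified through screening. The 19 is simply 13 / 0.70 rounded up, and the forecast of 32 eligible per month is well above it. It inherits the recruitment rounding and nothing more.

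**Conclusion.** The point holds in a limited form. On the literal text, delivering the stated sample on the stated timetable scores amber on recruitment, because 12.5 is below 13. The gap is 0.5 per month (0.5 / 12.5 = 4%), equivalent to two participants over 4 months or finishing about five days early. It matters only if true recruitment is near the planned rate. The result is amber, meaning amend and proceed with caution. Red would need, in addition, that no remediable change can be found.

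The conclusion assumes that observed rates are not rounded before scoring and that enrolment ends at 50. The probabilities further assume Poisson accrual at a constant rate and averaging to the 50th enrolment. The wording is still worth correcting, because this is a decision rule on a primary feasibility outcome and the change is free.

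**What to change.** In the green list of section 8.9, replace "Recruitment of at least 13 patients/month" with: *50 participants enrolled within 4 months of opening recruitment (mean at least 12.5/month, calculated to the date of the 50th enrolment, or over 4 months if 50 is not reached).* In part c, change the derived rate from 13 to 12.5 per month.

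For consistency only, restate the eligibility line as a mean of at least 18 per month while screening is open (12.5 / 0.70 = 17.86, rounded up).

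The cost is a wording change to two thresholds and one sentence, with no extra participants or data. The green line becomes slightly more lenient and then equals the sample and period the protocol already says it needs.
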